### Data collection and monitoring

2.9

Data collection will encompass a range of patient characteristics, including age, sex, height, weight, body mass index (BMI), ASA physical status, history of alcohol use and smoking, and Zubrod performance status (a preoperative measure of functional capacity and tolerance to treatment). Additional variables include percent predicted forced expiratory volume in 1 s (FEV1%), history of chronic obstructive pulmonary disease, cardiac conditions (including hypertension, coronary artery disease, previous myocardial infarction, and arrhythmias), diabetes, hepatic insufficiency, and renal insufficiency. Surgical details will encompass procedure type (1-wedge resection, 2-segmentectomy, 3-lobectomy), number of port sites (1-uniportal, 2-biportal), laterality (1-left, 2-right), duration of surgery, intraoperative blood loss, and duration of chest tube retention. All pertinent data will be meticulously recorded in case report forms (CRFs) and subsequently inputted into an electronic database under the vigilant supervision of the principal investigator (Table 1). An independent Data Monitoring Committee (DMC) will be tasked with the ongoing oversight of the data collection process. Upon completion of data registration, the electronic database will be safeguarded. De-identified datasets will then be forwarded to an independent statistician for comprehensive analysis in accordance with a predefined statistical plan. Any serious adverse events (SAEs), whether or not they are related to the study medication (e.g., persistent hemodynamic instability), must be promptly reported to the principal investigator. In such instances, the perioperative care team is obligated to implement necessary measures to safeguard participant well-being. Furthermore, these SAEs must be communicated to the DMC within a 24-h window for thorough discussion and to determine if any adjustments to the study interventions or the study’s discontinuation are warranted.

**Table 1 tab1:** Schedule of patients enrolment, study interventions, and outcome assessment.

Time point	Study period								
	Enrollment	Allocation	Post-allocation						Close-out
	Pre-op visit	Pre-op 1 day	Intra-op	6 h post-op	12 h post-op	24 h post-op	48 h post-op	72 h post-op	Discharged
Patient enrolment									
Eligibility criteria	×								
Written informed	×								
Consent									
Demographic data	×								
Baseline characteristics	×								
Randomization/allocation		×							
Study interventions									
Liposomal bupivacaine			×						
Ropivacaine & PCIA			×						
PCIA			×						
Outcome assessment									
QoR-15						×	×	×	
Pain-free interval				×	×	×	×	×	
VAS for pain at rest				×	×	×	×	×	
VAS for pain during cough				×	×	×	×	×	
Maximum VAS for pain						×	×	×	
First rescue analgesia				×	×	×	×	×	
Times of rescue analgesia				×	×	×	×	×	
Opioid consumption			×						×
NRS for anxiety						×	×	×	
NRS for sleep quality						×	×	×	
Analgesic Satisfaction									×
Incidence of PONV						×	×	×	
Severity of PONV						×	×	×	
Times of rescue antiemetic						×	×	×	
Confidence in coughing						×	×	×	
Confidence in ambulation						×	×	×	
Pneumothorax									×
Hemothorax									×
Drainage volume									×
Length of hospital stay									×
Adverse events									
Allergic			×	×	×	×	×	×	×
Total spinal anesthesia			×	×	×	×	×	×	×
Hypotension			×	×	×	×	×	×	×
Malignant arrhythmias			×	×	×	×	×	×	×
Cardiac arrest			×	×	×	×	×	×	×
Urinary retention			×	×	×	×	×	×	×
Puncture site infection			×	×	×	×	×	×	×
Pulmonary infection			×	×	×	×	×	×	××
Deep vein thrombosis			×	×	×	×	×	×	×
Pulmonary embolism			×	×	×	×	×	×	×
Atelectasis			×	×	×	×	×	×	×

According to SPIRIT, statement of defining standard protocol items for clinical trials.

Pre-op, preoperative; Intra-op, intraoperative; Post-op, postoperative; QoR-15, quality of recovery-15 scale; VAS, visual analogue scale; NRS, numerical rating scale; PCIA, patient-controlled intravenous analgesia pump; PONV, postoperative nausea and vomiting.

### Sample size calculation

2.10

The primary outcome will be the QoR-15 score, evaluated at 24, 48, and 72 h after surgery. Based on previously published data, the minimal clinically important difference (MCID) for the QoR-15 is set at 8 points (22), with an estimated standard deviation (SD) of 12 (23). Using an independent-sample *t*-test calculation with a two-sided alpha of 0.05 and 80% power (beta = 0.2), an initial sample size of 36 patients per group will be estimated to detect a statistically significant difference in mean QoR-15 scores. However, because the trial involves three groups and planned pairwise comparisons, a Bonferroni correction will be applied, adjusting the significance threshold to 0.017 (0.05/3). Additionally, since the primary outcome entails repeated measures over three time points, the sample size will be adjusted using an intraclass correlation coefficient (ICC) of 0.36, derived from pilot data. After these adjustments, a minimum of 48 participants per group will be required. The final sample size was calculated using the following formula for repeated measures: The formula is 
$n=\frac{{\left(Z_{1-a/2}+Z_{1-\beta }\right)}^{2}\times (1+(\kappa -1)\rho )\times \sigma^{2}}{\Delta^{2}\times (1-\rho )}$

*n* is the sample size required per group, 
κ
 is the number of repeated measurements (3 in this study), 
σ
 is the standard deviation (12), 
Δ
 is the minimal clinically important difference (8), and 
σ
 is the intraclass correlation coefficient (0.36). This number will then be inflated by 10% to account for potential attrition, loss to follow-up, or major missing data, resulting in a final sample size of 54 patients per group. Thus, a total of 162 patients (54 per group) will be enrolled.

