### Statistical analysis

2.11

The normality of continuous variables will be assessed using the Shapiro–Wilk test. Data following a normal distribution will be reported as mean (standard deviation, SD), while non-normally distributed data will be presented as median (interquartile range, IQR). Binomial variables will be expressed as proportions. The correlation structure will be selected based on the quasi-likelihood under the independence model criterion (QIC). Data distribution will determine the use of either a normal or gamma distribution with identity or log-link functions. The primary hypothesis of this study is that group L can demonstrate a superior quality of postoperative recovery compared to both control groups, with the difference being both statistically and clinically significant. A generalized estimating equation (GEE) model will be used to analyze repeated measures of continuous variables accounting for within-subject correlations. Continuous variables measured at a single time point will be analyzed using *t*-tests or Mann–Whitney U tests depending on normality and categorical data will be analyzed using the χ^2^ test. Post-hoc pairwise comparisons are strictly contingent on a significant overall between-group difference and *p*-values are adjusted using the Bonferroni method and set at 0.017. For longitudinal outcomes, this correction governs testing at both the individual time-point and overall treatment effect levels, ensuring robust control of the type I error rate. Statistical significance will be defined as *p* < 0.05.

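### The stated 48 per group cannot include both the Bonferroni and the ICC adjustment, and the printed formula does not fit a two-group comparison; the calculation needs restating, enrolment does not change

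*Protocol article*

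**What the plan says.** Section 2.10 of the protocol article builds the sample size in stages. It takes a difference of 8 points and an SD of 12 and, for a two-sample t-test "with a two-sided alpha of 0.05 and 80% power (beta = 0.2"), reports that "an initial sample size of 36 patients per group will be estimated". For the three planned pairwise comparisons it then describes "a Bonferroni correction will be applied, adjusting the significance threshold to 0.017 (0.05/3"), and for the three readings an adjustment by an ICC of 0.36 from pilot data. It concludes: "After these adjustments, a minimum of 48 participants per group will be required". The final size is attributed to this formula, with κ = 3 readings:

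n = (Z_{1−α/2} + Z_{1−β})² × (1 + (κ−1)ρ) × σ² / (Δ² × (1−ρ))

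A 10% allowance for attrition brings 48 to 54 per group, 162 in all.

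Section 2.11 says: "The primary hypothesis of this study is that group L can demonstrate a superior quality of postoperative recovery compared to both control groups". It adds that the difference should matter clinically as well as statistically. The corrected threshold applies both at individual time points and to the overall treatment effect.

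**The concern.** The text says two adjustments were made and names one formula as their source. A reader who enters the stated inputs should get 48, and does not. The formula itself also looks wrong for its purpose. Averaging three correlated readings should never require more patients than one reading does, yet this formula divides by (1−ICC), so n rises without limit as the ICC approaches 1.

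The sample size is the trial's main planning figure. As written it cannot be reproduced, and it does not tell the reader what power the trial has for its stated hypothesis, which names two controls.

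**Working it through.** **Inputs** (all from section 2.10): Δ = 8, σ = 12, κ = 3, ρ = 0.36, power 80% (Z = 0.842). Z_{1−α/2} is 1.960 at two-sided 0.05 and 2.394 at 0.05/3. The squared sums are 7.849 and 10.469.

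**1. The plan's other figures reproduce.**
- Initial size: 2 × 7.849 × 144/64 = 35.3, so 36.
- Attrition: 48/0.9 = 53.3, so 54.

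**2. The printed formula.** The multiplier is 1.72 × 144 / (64 × 0.64) = 6.047.
- At 0.05/3: 10.469 × 6.047 = 63.3, so 64 (63.0, also 64, at the rounded 0.017).
- At 0.05: 7.849 × 6.047 = 47.5, so 48.

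**3. The other route to 48.** The plain two-sample formula at 0.05/3 with no ICC term gives 2 × 10.469 × 144/64 = 47.1, so 48 (49 by exact t). Each route uses one of the two adjustments. The printed formula with both gives 64.

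**4. Does the formula fit the comparison?** For two groups compared on the mean of k readings, with σ the total SD at one reading:

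n = 2(Zα + Zβ)² × σ² × [1 + (k−1)ρ] / (k × Δ²)

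The printed version has no factor 2, does not divide by k, and adds 1/(1−ρ). At ρ = 0 and alpha 0.05 it gives 7.849 × 144/64 = 17.7, half the 35.3 behind the plan's own initial 36. The matching formula at 0.05/3 gives 47.1 × 1.72/3 = 27.0, so 28 per group.

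**5. Power of the planned size.** Two-sided 0.05/3, true difference 8 against each control, normal approximation. The SD of the three-day mean is 12 × √(1.72/3) = 9.09. With 48 evaluable per group:
- Single time point: SE = 12 × √(2/48) = 2.449; 8/2.449 − 2.394 = 0.872; power 81% per pair (79% by exact t).
- Three-day mean: SE = 9.09 × √(2/48) = 1.855; 8/1.855 − 2.394 = 1.919; power 97% per pair.

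The two comparisons share arm L and have equal n, so their test statistics correlate 0.5. Joint power is the bivariate normal probability that both succeed.

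| Evaluable per group | Contrast | Per pair | Both controls |
|---|---|---|---|
| 48 | Single time point | 79–81% | 70% |
| 48 | Three-day mean | 97% | 95% |
| 54 | Single time point | 85–86% | 77% |
| 54 | Three-day mean | 99% | 97% |

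**The case against.** Several counter-arguments deserve weight.

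- **Which adjustment is missing is unknown.** A reader might infer that the Bonferroni correction was left out, since the printed formula gives 48 at 0.05. Omitting the ICC from a Bonferroni-corrected two-sample calculation gives 48 equally well. The document does not settle it. What is established is only that both adjustments are not in the 48.
- **The size is adequate for the pairwise target.** A reader might infer that 64 per group (72 after attrition, 216 in total) was needed. That figure comes from a formula that does not fit the comparison, so it cannot serve as a benchmark. The 80% pairwise target is met closely at one time point and exceeded for the three-day mean.
- **The 80% was never claimed for beating both controls.** Section 2.10 attaches it to a two-sample difference, and pairwise powering is common in three-arm trials. This stands, so the joint power is information to add, not an error to correct. If success requires superiority over both controls, that rule by itself needs no alpha split between those two tests. At 0.05 each, joint power at one time point with 48 per group is 84%.
- **Dividing by (1−ICC) can be coherent** if the SD of 12 is a within-patient SD. The two-group formula then gives 27.0/0.64 = 42.2, so 43 per group, and 48 gives about 85% per pair and 76% for both on the three-day mean. The use of 12 in the initial t-test points to a total SD, but the text does not say. Even on this reading the printed formula lacks the factor 2/k.
- **Clinical significance is not defined as a hurdle.** A reader might take it to require an observed difference of at least 8. If the truth were exactly 8, that would succeed 50% of the time per pair and 33% for both, at any n. The reading is assumed, and the figures reveal no sample-size error.

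**Conclusion.** The stated calculation is wrong as written. The printed formula at the stated threshold gives 64, not 48, and 48 is reached with one adjustment only. The formula also does not match a two-group comparison of the mean of three readings.

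This does not make the trial too small. On the document's own inputs, the joint power falls below 80% only when a single time point is the target (70% with 48 evaluable, 77% with 54). For the three-day mean it is 95% or more. These figures assume a total SD of 12, equal correlation of 0.36 between readings, a true difference of 8 against each control, and two-sided 0.0167 per comparison. The point is a correction of the stated calculation and calls for no change in enrolment.

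**What to change.** Keep 54 per group. In section 2.10:

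1. State whether the primary contrast is the mean over 24, 48 and 72 h or each time point.
2. Replace the printed formula with the two-group formula in step 4 of the working, and say that SD 12 is the total between-patient SD at one time point. If it is a within-patient SD, recompute.
3. Drop the claim that 48 results from both adjustments. State instead the power of 48 evaluable per group at two-sided 0.0167 for a true difference of 8: about 97% per pair and 95% for both controls on the three-day mean, or about 80% and 70% at a single time point (about 85% and 77% with 54 evaluable).

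In section 2.11, add one sentence saying whether clinical significance is a pass/fail criterion or whether the 8-point difference serves to interpret the estimate and its interval. Settle this before results are seen.

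The cost is rewording section 2.10 and one sentence in 2.11. No further patients are needed.

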### Statistical analysis

2.11

The normality of continuous variables will be assessed using the Shapiro–Wilk test. Data following a normal distribution will be reported as mean (standard deviation, SD), while non-normally distributed data will be presented as median (interquartile range, IQR). Binomial variables will be expressed as proportions. The correlation structure will be selected based on the quasi-likelihood under the independence model criterion (QIC). Data distribution will determine the use of either a normal or gamma distribution with identity or log-link functions. The primary hypothesis of this study is that group L can demonstrate a superior quality of postoperative recovery compared to both control groups, with the difference being both statistically and clinically significant. A generalized estimating equation (GEE) model will be used to analyze repeated measures of continuous variables accounting for within-subject correlations. Continuous variables measured at a single time point will be analyzed using *t*-tests or Mann–Whitney U tests depending on normality and categorical data will be analyzed using the χ^2^ test. Post-hoc pairwise comparisons are strictly contingent on a significant overall between-group difference and *p*-values are adjusted using the Bonferroni method and set at 0.017. For longitudinal outcomes, this correction governs testing at both the individual time-point and overall treatment effect levels, ensuring robust control of the type I error rate. Statistical significance will be defined as *p* < 0.05.

All study outcomes will be analyzed in the modified intentiontotreat (mITT) population, including all patients who are randomized, received the assigned intervention, and completed all or part of the postoperative follow-up assessments. Patients will be included in the analysis according to their original allocation. To evaluate the robustness of the primary outcome and its sensitivity to protocol deviations, a per-protocol (PP) analysis will be performed as a sensitivity analysis to verify the reliability of the findings from the intention-to-treat analysis. Multiple testing correction will be applied to primary and secondary outcome measures where applicable. As a theoretical principle, this adjustment is generally not applied to safety indicators. Odds ratios (OR) and corresponding 95% confidence intervals (CI) will be reported where appropriate. No interim analysis will be planned. Missing data will not be imputed. Statistical analyses will be performed using SPSS (version 25.0; IBM SPSS). A two-sided *p*-value < 0.05 will indicate statistical significance, except where false discovery rate (FDR) corrections apply.

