### Secondary outcomes

2.5

Secondary outcomes will include the pain-free interval (defined as the time from the end of surgery to the first onset of pain), resting and cough-evoked pain Visual Analog Scale (VAS) scores (ranging from 0, no pain, to 10, worst imaginable pain) assessed at 6, 12, 24, 48, and 72 h postoperatively; maximum pain scores at 24, 48, and 72 h; intraoperative and total postoperative opioid consumption; time from the end of surgery to first request for rescue analgesia and the number of such requests; anxiety and sleep quality (using numeric rating scores, NRS, 0–10, higher indicating greater anxiety/ greater sleep) at 24, 48, and 72 h; patient satisfaction with analgesia measured using an NRS (0–10, higher indicating greater satisfaction); incidence and severity of postoperative nausea and vomiting (PONV), graded on a 4-point scale (0 = none, 1 = nausea only, 2 = 1–3 vomiting episodes, 3 = ≥4 episodes) and the number of rescue antiemetic administrations at 24, 48, and 72 h; as well as patient confidence in coughing and ambulation, both assessed using an NRS (0 = no confidence to 10 = full confidence). All postoperative assessments will be performed daily at 17:00 until 3 days after surgery. The following outcomes will be recorded prior to patient discharge: the incidence of pneumothorax or hemothorax during the entire postoperative period, total postoperative drainage volume, and length of hospital stay.

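### The distribution and link of the GEE are left to the observed data, so the primary effect scale is not fixed in QoR-15 points, and gamma is allowed for 0-10 scores that include 0

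*Protocol article*

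**What the plan says.** The Statistical analysis section (2.11) of the protocol article assigns repeated continuous outcomes to one type of model: "A generalized estimating equation (GEE) model will be used to analyze repeated measures of continuous variables accounting for within-subject correlations". For that model it states: "Data distribution will determine the use of either a normal or gamma distribution with identity or log-link functions". It gives no criterion for the choice and makes no exception for the primary outcome. The working correlation is also to be chosen from the data, by QIC.

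The same section words the primary hypothesis as superiority of group L over both control groups, "with the difference being both statistically and clinically significant". The Sample size calculation section (2.10) says what clinically significant means: the "minimal clinically important difference (MCID) for the QoR-15 is set at 8 points", with an SD of 12.

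The Secondary outcomes section (2.5) defines resting and cough pain as VAS scores "ranging from 0, no pain, to 10, worst imaginable pain", measured at 6, 12, 24, 48 and 72 h. Anxiety, sleep quality and confidence in coughing and ambulation are numeric ratings from 0 to 10, which Table 1 schedules at 24, 48 and 72 h. All of these are repeated measures, so they fall under the same rule.

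**The concern.** This is a rule that the article states, not a detail left to a later plan. An analysis plan that follows it inherits a choice made after the outcomes are seen; one that fixes the model departs from it.

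Two consequences follow. First, the link determines the effect measure. The primary result could turn out to be a difference in points or a ratio of means, although the hypothesis and the sample size are stated in points. The trial is open-label, which makes it more important that the primary effect measure is settled beforehand.

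Second, a gamma distribution is defined only for values above 0. On the pain scale, 0 is a valid reading and the one the treatment aims for. Skewed pain scores are also where a rule driven by the data distribution would most likely select gamma. If zeros were then dropped or altered to make the model fit, readings would be lost unevenly between groups and the comparison would be biased.

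**Working it through.** **1. The trial is planned on the point scale.** Inputs from section 2.10: difference 8, SD 12, two-sided alpha 0.05, power 80%. The initial size per group is 2(z₀.₉₇₅ + z₀.₈₀)² × SD² / difference² = 2 × (1.960 + 0.842)² × 144/64 = 2 × 7.849 × 2.25 = 35.3, rounded up to 36. This is the article's own initial figure. The target is therefore an absolute difference in QoR-15 points.

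**2. What the four permitted combinations report.** One simulated QoR-15 data set (54 per arm, SD 12, ICC 0.36, three visits) was fitted under each combination. Contrasts are group R and group P against group L.

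| Distribution / link | R vs L | P vs L | Scale |
|---|---|---|---|
| Normal / identity | -6.45 | -7.25 | points |
| Gamma / identity | -6.46 | -7.27 | points |
| Normal / log | -0.0548 | -0.0619 | log ratio |
| Gamma / log | -0.0550 | -0.0621 | log ratio |

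The link, not the distribution, changes the scale. The log-link contrasts correspond to ratios of exp(-0.0548) = 0.947 and exp(-0.0619) = 0.940.

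**3. The 8-point threshold under a log link.** The ratio is (m + 8)/m for comparator mean m. The article gives no mean, so m is assumed.

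| m | Ratio equal to 8 points | Points equal to a ratio of 1.07 |
|---|---|---|
| 90 | 1.089 | 6.3 |
| 100 | 1.080 | 7.0 |
| 110 | 1.073 | 7.7 |
| 120 | 1.067 | 8.4 |
| 130 | 1.062 | 9.1 |

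One and the same ratio falls below or above 8 points depending on the comparator mean.

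**4. Effect on the primary test.** One pairwise contrast of three-visit means was simulated under equal means (54 per arm, SD 12, ICC 0.36, alpha 0.05/3, 40,000 runs; assumed means 90, 110 and 130; normal data). Type I error was about 0.019 with either link. Always taking the more favourable link raised it by about 0.0002. The two links disagreed on significance in under 0.05% of null trials, and in under 0.25% at true differences of 4 or 8 points. A repeat of this simulation with a different random seed agreed.

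**5. Zeros in the 0-10 scores.** The gamma log-density at 0 is minus infinity (checked for shape 2). Illustrative VAS data were simulated for three arms of 54 with three readings each; the shares of zeros are a product of assumed inputs.

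| | L | R | P |
|---|---|---|---|
| Share of zeros | 34.6% | 27.8% | 18.5% |
| Mean, all readings | 1.20 | 1.59 | 1.91 |
| Mean, readings above 0 | 1.84 | 2.20 | 2.34 |

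The gamma/log estimating equations could be solved with zeros kept: log ratios 0.273 (R to L) and 0.463 (P to L), that is, ratios of 1.31 and 1.59. With zeros dropped they were 0.161 and 0.240, that is, 1.17 and 1.27. The P minus L difference in raw means falls from 1.91 - 1.20 = 0.71 to 2.34 - 1.84 = 0.50. The loss works against the arm with more pain-free readings.

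**The case against.** The strongest reply is that little harm to the primary test has been shown. Identity and log links test the same null hypothesis of equal means, and step 4 finds almost no difference between them. Fitted means from a log-link model can be converted back to points and then set against 8. An independent statistician is to work from a predefined plan (section 2.9), and normal with identity link is already among the permitted options. All of this stands, and it limits the primary concern to the effect scale. But the article provides no back-conversion step, and the rule it states is itself data-dependent.

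A reader might infer several stronger points that the documents do not support:

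- **That gamma cannot give a difference in points.** With an identity link it does (step 2).
- **That a log link excludes zeros.** A normal/log model fitted the VAS data with 19% to 35% zeros per arm.
- **That zeros threaten the primary outcome.** A QoR-15 total of 0 needs all 15 items at their worst value, which is not realistic.
- **That zeros will be dropped.** No passage says so. The bias in step 5 is conditional on that handling.
- **That the model ignores the baseline data collected.** Section 2.11 names no covariates and excludes none. A covariate list is commonly left to the full protocol or analysis plan, and an unadjusted randomized comparison is valid, only less precise.

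**Conclusion.** The concern holds in a limited form, and the text should be changed. For QoR-15, the article leaves the effect measure to the observed data although its hypothesis and its 8-point threshold are in points. The matter is one of pre-specification and interpretation; the effect on type I error is probably negligible, at about 0.0002 under the assumptions of step 4 (normal data, assumed means).

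For the repeated 0-10 secondary scores, gamma is an unsuitable option because 0 is a valid and desired reading. The size of any bias depends on how many zeros occur and how they are handled, neither of which the article gives. The fall from 1.59 to 1.27 shows that it can matter; it is not a forecast for this trial.

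**What to change.** Replace the sentence on distribution and link with a fixed rule:

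- QoR-15 and the repeated 0-10 scores will be analysed by GEE with a normal distribution, identity link and robust standard errors.
- Contrasts will be reported in points with confidence intervals, and for QoR-15 set against the 8-point MCID.
- Other distributions or links will serve only as sensitivity analyses.
- Gamma will not be used for any score that can be 0.

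With robust standard errors, inference on the mean difference does not depend on normally distributed scores. The downside is possibly slightly less efficiency for skewed scores. The cost is a sentence or two of analysis text, with no new data and no change to the sample size.

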An emergency response team will be established in this study to promptly manage patients with breakthrough severe pain and nausea/vomiting, ensuring rapid symptom relief. The acute pain management protocol will include acetaminophen and oxycodone: initially, 1 g of intravenous acetaminophen will be administered every 6 h (maximum daily dose not exceeding 4 g). If the patient experiences intolerable pain (Visual Analog Scale score > 4) for more than 30 min, or if the maximum daily dose of acetaminophen has been reached, oral oxycodone 5 mg will be administered instead, with dose adjustments within the safe range as needed. Subsequent doses may be repeated every 4 to 6 h under close monitoring and strict control of dosage variations. For participants in groups R and P using PCIA, rescue analgesia will be implemented according to a tiered protocol. If intolerable pain occurs despite the preset continuous sufentanil background infusion, PCIA bolus doses will be administered as the first-line rescue strategy. Should pain remain uncontrolled after reaching the maximum allowable bolus dose, the subsequent, predefined rescue analgesic protocol will then be initiated. For acute episodes of severe nausea and vomiting, potential underlying causes will first be assessed to exclude gastrointestinal symptoms resulting from other primary conditions. Once other causes are ruled out, ondansetron 4 mg will be administered intravenously as rescue therapy (maximum daily dose not exceeding 16 mg). Dosage adjustments may be made based on symptom severity within established safety limits.

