The distinctive feature of the group L in this trial is its independence from both indwelling catheters and opioid reliance, representing a key divergence from conventional analgesic strategies. This approach may demonstrate advantages by circumventing drawbacks associated with catheter placement and opioid dependence. The primary objective of this design is to directly evaluate the impact of a single-injection thoracic paravertebral block using liposomal bupivacaine on the quality of postoperative recovery, with particular emphasis on the quality of postoperative pain management provided by this strategy. The three-arm trial design enables comparison across two distinct dimensions. The first comparator is the most fundamental opioid-dependent PCIA, representing baseline postoperative pain management. When administered within safe dosing parameters, PCIA can meet essential analgesic requirements for pain relief. The second comparator combines PCIA with a ropivacaine-based thoracic paravertebral block, constituting a more advanced pain management protocol designed to achieve comprehensive analgesia. This experimental design addresses two fundamental questions: whether the single-injection thoracic PVB using liposomal bupivacaine can fulfill the basic requirements of postoperative pain management, and what level of analgesic efficacy it can provide.

Conventional analgesic agents, including intravenous analgesics and local anesthetics, have half-lives insufficient to cover the entire postoperative recovery period. As a result, catheter-based techniques—such as continuous epidural, intravenous, or regional nerve block analgesia—remain widely used in postoperative pain management, despite introducing risks and inconveniences related to catheter placement. Liposomal bupivacaine represents a novel long-acting, sustained-release local anesthetic. The drug is encapsulated within multivesicular phospholipid vesicles, enabling controlled and prolonged release of bupivacaine. Pharmacodynamically, peak plasma concentrations are typically achieved within 30 min after local injection, with analgesic effects lasting up to 72 h (20). Notably, ERAS guidelines emphasize that postoperative analgesia should be initiated preemptively—before pain onset—and maintained effectively (24). Therefore, liposomal bupivacaine emerges as a promising option that may potentially revolutionize postoperative pain management paradigms.

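### Pain-free interval and time to first rescue request are time-to-event outcomes, but section 2.11 names no method for them and gives no rule for patients without the event by 72 h

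*Protocol article*

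**What the plan says.** Section 2.5 of the protocol article lists the pain-free interval, "defined as the time from the end of surgery to the first onset of pain", and the "time from the end of surgery to first request for rescue analgesia and the number of such requests". On follow-up it states: "All postoperative assessments will be performed daily at 17:00 until 3 days after surgery". Table 1 schedules both outcomes at 6, 12, 24, 48 and 72 h and not afterwards.

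Section 2.11 chooses tests by type of variable:
- A GEE model "will be used to analyze repeated measures of continuous variables accounting for within-subject correlations".
- For one value per patient: "Continuous variables measured at a single time point will be analyzed using" t-tests or Mann-Whitney tests, depending on normality.
- For categorical data, a chi-square test.

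It does not mention Kaplan-Meier, log-rank, Cox or censoring. It adds: "Missing data will not be imputed". It also says that every outcome is analysed in the modified intention-to-treat population: patients who were randomised, received their intervention and had at least some follow-up.

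**The concern.** A patient who reaches 72 h without pain, or without asking for rescue, has no event time. The article's own rationale makes such patients plausible. The Discussion describes liposomal bupivacaine "with analgesic effects lasting up to 72 h", which is as long as the follow-up window. Rescue is given on demand, by a team set up to "promptly manage patients with breakthrough severe pain and nausea/vomiting" (section 2.8), so some patients may never need it. If the trial's hypothesis is right, more of these patients will be in group L.

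If patients without an event time are left out, the comparison is restricted to patients in whom analgesia failed. That restriction conditions on a post-randomisation event which treatment affects, so the protection of randomisation is lost. The difference between arms shrinks, because the longest times are removed and more of them come from the better arm. Both outcomes bear directly on whether the block can stand alone as an analgesic strategy, which is one of the article's stated questions.

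**Working it through.** **Which listed method applies.** Each outcome gives one time per patient. It is not a repeated measure, so GEE does not fit, and it is not categorical, so chi-square does not fit. Only the t-test/Mann-Whitney line remains.

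**What happens to event-free patients.** No value is defined for them and missing values are not filled in, so literally they contribute nothing. This conflicts with the statement that all outcomes use the full modified intention-to-treat set.

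**Inputs.**
- From the article: 72 h window; pairwise threshold 0.05/3, about 0.017; 48 evaluable patients per group (54 before attrition).
- Assumed: exponential event times and the event-free shares at 72 h. The article gives neither, so a range is shown. It also has no figure of its own on this point to reproduce.

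**Formulas.** For an event-free share p at 72 h:
- Hazard: λ = −ln(p)/72.
- True median: ln(2)/λ.
- Median among patients with the event by 72 h: −ln(1 − (1 − p)/2)/λ.

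**Worked case, 50% (L) versus 25% (P) event-free.**
- λ_L = 0.6931/72 = 0.00963 per h; λ_P = 1.3863/72 = 0.01925 per h; hazard ratio 0.5.
- True medians: 0.6931/0.00963 = 72 h and 0.6931/0.01925 = 36 h, a gap of 36 h.
- Medians among patients with the event: −ln(0.75)/0.00963 = 29.9 h and −ln(0.625)/0.01925 = 24.4 h, a gap of 5.5 h.
- Patients left on average: 48 × 0.50 = 24 and 48 × 0.75 = 36.

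**Power by simulation** (48 per arm, two-sided 0.05/3; repeat runs agree to within about 2 points):

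| Event-free, L vs control | Mann-Whitney, event-free dropped | Mann-Whitney, event-free ranked at 72 h | Log-rank, censored at 72 h |
|---|---|---|---|
| 50% vs 25% | 5% | 56% | 61% |
| 10% vs 1% | 45% | 67% | 80% |
| 5% vs 0.1% | 78% | 87% | 95% |

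**A second pattern.** Suppose the arms differ only in the share who never have the event, with the same distribution of times among those who do (54 per arm, threshold 0.017, 2,000 runs). Dropping event-free patients then rejects in 1.6% to 1.9% of trials, which is only the test's own error rate. At 50% versus 20% event-free, ranking at 72 h gives 64% and log-rank 78%. At 10% versus 1% the figures are 5% and 15%.

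**The case against.** The strongest reply has four parts.

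1. Section 2.11 never names these two outcomes, and Table 1 lists them at five time points, so the label of a single time point is not a clean fit. This stands: the assignment is an inference by elimination. A reader might take it that the plan expressly assigns a Mann-Whitney test to these outcomes; it does not.

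2. No sentence excludes event-free patients. Someone followed to 72 h without the event is fully observed, so recording 72 h need not count as imputation, and the population statement points toward keeping everyone. This also stands. Exclusion is the literal result of having no value and no imputation, not a declared rule. The table shows that most of the collapse at high event-free shares comes from dropping patients and not from Mann-Whitney itself: ranking at 72 h recovers much of the loss. But the article gives no such rule, and a t-test or mean on values cut at 72 h would still be biased.

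3. The event-free shares are assumed. For the pain-free interval they are probably low, since the Introduction says that these patients still have moderate to severe pain. This stands and limits the size claimed.

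4. An article condenses a fuller plan, which may name survival methods. This carries less weight, because the article does more than stay silent. It fixes tests by variable type and adds a no-imputation rule, and together these handle censored times badly.

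**Conclusion.** The point holds at moderate severity. Section 2.11 provides no suitable method for two time-to-event secondary outcomes, and its literal reading removes treatment successes and biases the comparison toward no difference.

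The size rests on assumed exponential times and assumed event-free shares. The loss against log-rank runs from about 17 points of power (78% vs 95%) when few patients are event-free to about 56 points (5% vs 61%) when many are. It is probably larger for first rescue than for the pain-free interval.

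A reader might infer that almost all power is lost on the pain-free interval, the first-listed secondary outcome. The documents do not support that: they give no event-free share, and at the low shares more plausible for that outcome the loss is real but partial. The primary QoR-15 analysis is not affected.

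**What to change.** In section 2.11, state that the pain-free interval and the time to first rescue request are analysed as time-to-event outcomes from the end of surgery. Patients without the event are censored at 72 h, or at their last assessment if earlier. Present Kaplan-Meier curves, and use log-rank tests with Cox hazard ratios for L vs P and L vs R under the existing 0.017 pairwise threshold.

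The cost is a change of wording, with no new data and no change to the sample size. Making it before the data are analysed also removes a later choice between dropping, capping and censoring, which the table shows can give very different answers.
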